### Patient Reported Outcome Measures (PROM)

PROM will consist of (1) Stroke Impact Scale, (2) health related quality of life: EQ-5 D at one year in those who completed questionnaire at the baseline, (3) modified RANKIN, (4) Barthel score and (5) health service use.

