**Methods/Design:**

We will conduct a cohort study in eight acute NHS trusts within East of England, with at least one year of follow-up after stroke. The study population will be a systematically selected representative sample of patients admitted with stroke during the study period, recruited within each hospital. We will collect individual patient data on prognostic characteristics, health care received, outcomes and costs of care and we will also record relevant characteristics of each provider organisation. The determinants of one year outcome including patient reported outcome will be assessed statistically with proportional hazards regression models. Self (or proxy) completed EuroQol (EQ-5D) questionnaires will measure quality of life at baseline and follow-up for cost utility analyses.

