### Sample Population

For the first component, the sample population will be stroke patients who are admitted to any of the hospitals within the Anglia region of Stroke & Heart Clinical Network between October 2009 and September 2011. Baseline data are already recorded, prior to the study commencement, as part of routine clinical data collection by Anglia Stroke Clinical Network (as described in detail below). The study sample will be a systematically selected sample (every third month) rather than a consecutive cohort of patients admitted to eight acute NHS hospital trusts. Therefore, this is not a consecutive case study; instead it seeks to be representative of the catchment population of the hospital and has taken into account the seasonal variation in stroke incidence and outcome [13].

For the patient reported outcome component of the study the following inclusion and exclusion criteria will be used. Inclusion criteria are (1) age > = 18 years, (2) admitted to hospital with stroke (diagnosed by stroke physicians) during the study months, (3) able to provide informed consent or patient's personal consultee agrees to study participation. Exclusion criteria include (1) age <18 years, (2) patients with pre-existing diagnosis of dementia (for PROM component only).

The Anglia Stroke Network was funded through the NHS Improvement Programme, following the publication of the National Stroke Strategy in December 2007. The Network was established in April 2008 to support the development of stroke services in Norfolk, Suffolk and Cambridgeshire regions. Since its inception, the Network regularly collected data to capture clinical service activities of the eight acute hospital trusts in the Network for the purpose of monitoring of services benchmarked by National targets and guidance from National Institute of Health & Clinical Excellence (NICE) in England and Wales. Data collection commenced in January 2009 and involves the individual trusts collecting clinical data which is fed back to the network by monthly reports. The total number of strokes admitted to the 8 acute trusts within the Network is approximately 4,000 per annum in 2009. The stroke cases were identified prospectively data were collected by the clinical team who looked after the patients and anonymised raw clinical data were sent to the network on monthly basis. The network collates and analyses the data for above mentioned purposes.

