### Statistical analysis

Quantitative data will be analysed by multivariate Cox-proportional hazards to examine the relationships between different aspects of health services and time to death, adjusting for prognostic characteristics. Multiple logistic or linear regression models will be constructed as appropriate for dichotomised and continuous outcome variables respectively. T tests for normally distributed data and Mann-Whitney U tests for non-normally distributed data will be used to compare continuous outcomes. Volume-outcome relationships will be investigated. Missing prognostic and EQ-5 D data will be imputed, based on each patient's other prognostic characteristics. Clustering of data by hospital trust will be investigated and, if necessary, taken into account, and intra-class correlation coefficients calculated to inform future research.

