#### Outcome

As the National Institute of Health and Clinical Excellence [18] recommends use of the EQ-5 D [17] within cost-effectiveness analysis this will be our primary measure within the economic analyses. EQ-5 D data will be collected at two University Hospitals and two district general hospitals within the clinical network. We will use "mapping" strategy to estimate the cost-effectiveness analyses across the region. The use of mapping, where scores from a condition-specific (non preference-based) measure are 'converted' into a utility (preference-based) score using a pre-defined formulae, has been advocated (in certain instances) by the UK National Institute of Health and Clinical Excellence (NICE) [18], and has been used to estimate the utility scores, and in turn cost-effectiveness, of a number of health care interventions [19]. Mapping presents the possibility of not asking all participants to complete the EQ-5 D. In this study we propose to take advantage of this by developing a mapping algorithm based on the response from participants participating in this component to predict the EQ-5 D for participants in retrospective cohorts and those who did not participate in PROM component.

Because the quality of life measure (EQ-5D) which can be used to estimate health utility and calculate QALYs (Quality Adjusted Life Years) for economic evaluation is outside the remit of routine data collection and cannot be done retrospectively, we will collect EQ-5 D data in only the second year of the study (October 2010 and January, April and July 2011 cohorts and one year follow up data to be collected September and December 2011, and March and June 2012) in those who provide informed consent to the study (we estimate that the sample will be approximately 15-20% of the whole sample after excluding the one year pre-study period (between October 2009-September 2010) and after taking into account of refusal rate (estimated ~ 30%) in trusts with Stroke or Comprehensive Local Research Network Research Nurses.

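### The one-year EQ-5D is limited to patients with a completed baseline questionnaire, an avoidable selection step that may under-represent more severe survivors in the EQ-5D and cost-utility analyses

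*Protocol article*

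**What the plan says.** The section Patient Reported Outcome Measures (PROM) lists five items. The second is "EQ-5 D at one year in those who completed questionnaire at the baseline". The Stroke Impact Scale, modified Rankin, Barthel score and health service use carry no such condition.

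Other parts of the protocol article bear on who would be affected:

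- **Abstract, Methods/Design:** "Self (or proxy) completed EuroQol (EQ-5D) questionnaires will measure quality of life at baseline and follow-up for cost utility analyses". A proxy may therefore answer at baseline as well as later.
- **Sample Population:** entry to the PROM component requires a patient to be "able to provide informed consent or patient's personal consultee agrees to study participation". The stated exclusions are age under 18 and a prior dementia diagnosis. Stroke severity is not an exclusion.
- **Statistical analysis:** "Missing prognostic and EQ-5 D data will be imputed, based on each patient's other prognostic characteristics".
- **Economic evaluation, including its Outcome subsection:** EQ-5D is the main effectiveness measure, with responses sought at baseline and 12 months. It is collected in four of the eight trusts, in the second-year cohorts, from consenting patients. A mapping algorithm built on these respondents is then used "to predict the EQ-5 D for participants in retrospective cohorts and those who did not participate in PROM component".

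**The concern.** The condition is a stated rule, not a detail left to a fuller document. A patient may enter the PROM component, miss the acute-phase form, and still be followed at one year for the Stroke Impact Scale, Rankin, Barthel and service use, yet fall outside the one-year EQ-5D. One missed form during the admission becomes a permanent loss of the more informative later value.

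Failure to obtain a baseline form in acute stroke may plausibly depend on severity, on whether a relative is present, and on research-nurse time at the trust. If so, three things are at stake:

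- the level of one-year utility among survivors would look better than it is;
- a comparison between services would be distorted if completion differs between them;
- the mapping model would lose usable one-year pairs, possibly at the severe end of the scale. Mapping needs the condition-specific score and the EQ-5D at the same time point. It does not need a baseline EQ-5D.

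A missing baseline does not justify the loss, because the plan already says that "Missing prognostic and EQ-5 D data will be imputed".

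**Working it through.** **1. Reproduce the plan's own EQ-5D sample.** Inputs from Plan of investigation and Outcome: cohort about 2,400; 4 of 8 study months; 4 of 8 trusts; refusal about 30%. Equal trust volumes are assumed.

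2,400 × 0.5 × 0.5 × 0.70 = 420, and 420 / 2,400 = 17.5%.

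This lies inside the stated 15-20%. If the four trusts hold 40% to 60% of volume (assumption), the result is 336 to 504, or 14% to 21%.

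**2. Overstatement of mean utility among survivors.** The article gives no completion rates and no utility values, so everything here is assumed: 80% of baseline completers and 60% of non-completers alive at one year, and survivors' utility 0.2 lower in non-completers. With non-completion m:

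- non-completers as a share of survivors: s = 0.6m / (0.6m + 0.8(1 − m))
- overstatement of the survivor mean: 0.2 × s

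| m | s | Overstatement |
|---|---|---|
| 5% | 0.03 / (0.03 + 0.76) = 3.8% | 0.008 |
| 10% | 0.06 / (0.06 + 0.72) = 7.7% | 0.015 |
| 20% | 0.12 / (0.12 + 0.64) = 15.8% | 0.032 |

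One trust at 5% and another at 20% give a spurious difference of 0.2 × (0.158 − 0.038) = 0.024 among survivors.

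**3. The same contrast per patient, with deaths counted as zero.** Deaths are to be known for everyone, so only survivors' utility is wrong. The overstatement is 0.6m × 0.2: 0.006 at 5% and 0.024 at 20%. The difference is 0.018.

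**4. A yardstick on the per-patient basis.** The Sample size section illustrates HR 0.76 from 20% one-year mortality. The second group's mortality is 1 − 0.80^0.76 = 15.6%, a gap of 4.4 points. At an assumed utility of 0.6 this is worth 0.044 × 0.6 = 0.026. The like-for-like ratio is 0.018 / 0.026, about 70%.

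**5. Wider range.** Let the utility gap be 0.1 to 0.3, with non-completion expressed as a share of survivors:

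- 30% in both services: each mean shifts by 0.03 to 0.09, and the difference between services by 0.
- 25% against 35%: the difference shifts by 0.01 to 0.03.
- 20% against 40%: the difference shifts by 0.02 to 0.06.

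All figures are before case-mix adjustment, imputation or mapping.

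**6. Cost of collecting the missing forms.** Using 420 participants, 10-20% non-completion and 60% survival: 420 × 0.10 × 0.6 = 25 and 420 × 0.20 × 0.6 = 50.

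**The case against.** The strongest reply is that the article already provides for ill patients. A proxy can complete the baseline form, and a patient who cannot consent can enter if a "personal consultee agrees to study participation". A reader might infer from the rule that everyone too ill at baseline is removed. The documents do not support that: only patients with neither a self nor a proxy baseline response are affected, and nothing shows that they are the most disabled. This part stands and limits the point to a risk. It is weakened a little because the Outcome subsection speaks only of informed consent for the EQ-5D and does not repeat the consultee route.

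Second, the PROM list is terse, and the phrase may simply describe the paired cohort. That is possible. But the Economic evaluation refers back to what was said earlier about 12-month responses and does not clearly override the condition. If shorthand was meant, one sentence settles it.

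Third, imputation and mapping keep affected patients in the cost-utility analysis. This is partly right. Imputation from prognostic characteristics works only as far as those characteristics explain the missingness, and the mapping is trained on the same selected group. Equally, selection harms the mapping only if the relation between score and EQ-5D differs in non-completers, or if part of the score range is thin. Neither is shown.

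Fourth, any bias may be small beside the noise. With 420 / 4 = 105 participants and roughly 80 survivors per trust, and an assumed SD of 0.3, the standard error of a two-trust difference is 0.3 × √(2/80) = 0.047. The illustrated 0.024 is about half of that. This is fair for a study that calls itself exploratory and disclaims causal inference. It argues for modest weight, but not for keeping a restriction that saves almost nothing.

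**Conclusion.** The point holds as an avoidable selection risk in the one-year EQ-5D, and through it in the cost-utility analysis and the mapping data. Followed as written, the rule discards usable one-year values of the main economic effectiveness measure.

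Its size cannot be computed from the article. The 0.024 among survivors and 0.018 per patient rest entirely on the assumed survival rates, utility gap and 5% against 20% contrast.

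Three stronger readings should be resisted:

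- **That the comparisons between services are biased.** With a common utility gap, equal non-completion among survivors leaves the difference unchanged, and no passage shows that completion differs by service.
- **That the bias is as large as the utility value of the illustrated hazard ratio.** That sets a survivor-only figure against a per-patient one. On the same basis it is about 70%, before any adjustment.
- **That all patient-reported outcomes are affected.** The condition sits on the EQ-5D alone. One-year mortality, the primary outcome, and the sample size and power figures do not depend on it.

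This is a cheap improvement, not a demonstrated flaw in the results.

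**What to change.** In the PROM section, delete the baseline-completion condition. State that the one-year EQ-5D, self or proxy, is sought from every PROM participant alive at one year, within the telephone and postal follow-up already planned. Impute missing baseline EQ-5D under the existing plan in Statistical analysis, and report the analysis restricted to baseline completers as a sensitivity analysis. Tabulate baseline completion by trust, and compare the characteristics of completers and non-completers, so that differential completion can be seen. Reconcile the consent wording in the Outcome subsection with the consultee route in Sample Population.

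The cost is roughly 25 to 50 extra questionnaires on the assumptions above. The downside is reliance on some imputed baseline values, which the sensitivity analysis makes visible.

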### Statistical analysis

Quantitative data will be analysed by multivariate Cox-proportional hazards to examine the relationships between different aspects of health services and time to death, adjusting for prognostic characteristics. Multiple logistic or linear regression models will be constructed as appropriate for dichotomised and continuous outcome variables respectively. T tests for normally distributed data and Mann-Whitney U tests for non-normally distributed data will be used to compare continuous outcomes. Volume-outcome relationships will be investigated. Missing prognostic and EQ-5 D data will be imputed, based on each patient's other prognostic characteristics. Clustering of data by hospital trust will be investigated and, if necessary, taken into account, and intra-class correlation coefficients calculated to inform future research.

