### Sample size

Since this is an exploratory study designed to provide information for further analytic research, sample size will be determined partly pragmatically rather than on particular hypothesis tests. For illustration purposes, a total sample of 2264 patients would provide 80% power to detect a constant Hazard ratio (HR) of 0.76 for one-year mortality between two groups of roughly equal size, based on the log-rank test. This assumes a 20% one-year mortality rate in the reference group, no loss to follow-up before one year and 2-sided type I error of 5%. If one-year mortality is 30%, then 2264 patients would provide 76% power to detect a HR of 0.81.

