### Outcome measurements

Primary outcome of the study will be one year mortality comparison between services with different characteristics. The secondary outcomes will include (1) final discharge destination (good or poor outcome) [16], (2) length of acute hospital stay, (3) length of stay in rehabilitation, (4) complications during acute and rehab-hospital stay and significant procedures (e.g. aspiration pneumonia, myocardial infarction), (5) readmissions, (6) composite cardiovascular events (recurrent TIA/Stroke/Acute Coronary Syndrome, Myocardial infarction).

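### Length of stay is analysed by methods with no term for in-hospital death, so a service with more early deaths can appear to have shorter stays

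*Protocol article*

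**What the plan says.** The Outcome measurements section of the protocol article makes one-year mortality, compared between services, the primary outcome. Its secondary outcomes include "2) length of acute hospital stay, (3) length of stay in rehabilitation" and, further down the list, "5) readmissions, (6) composite cardiovascular events (recurrent TIA/Stroke/Acute Coronary Syndrome, Myocardial infarction".

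The Statistical analysis section names one time-to-event method, "multivariate Cox-proportional hazards to examine the relationships between different aspects of health services and time to death". Other outcomes are assigned by data type: "Multiple logistic or linear regression models will be constructed as appropriate for dichotomised and continuous outcome variables respectively". It then adds: "T tests for normally distributed data and Mann-Whitney U tests for non-normally distributed data will be used to compare continuous outcomes". Length of stay is not named there, but as a continuous outcome it falls under linear regression and the t or Mann-Whitney test. No section says how a patient who dies in hospital enters the length-of-stay analysis.

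Two other places bear on the point. The Sample size section works with substantial mortality: "This assumes a 20% one-year mortality rate in the reference group", with 30% as the alternative. The Background names length of stay in the study hypothesis, and the Discussion sets it next to mortality among the outcomes by which the best services are to be recognised.

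**The concern.** A hospital stay can end in discharge alive or in death. A t test, a Mann-Whitney test or a linear model applied to days in hospital does not distinguish the two. If deaths enter at face value, an early death is a short stay. If they are left out, the comparison is restricted to survivors, and who survives may itself depend on the service.

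This would matter little if services had similar mortality, but the study is built to find mortality differences. Where they exist, length of stay can move in the apparently favourable direction for the worse service. Adjustment for baseline prognosis does not cure this, because the death occurs after admission and is part of the outcome process. The reader at risk is a commissioner or trust that takes a shorter stay as a sign of a better service.

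**Working it through.** **The plan's own figures.** The Sample size section says "a total sample of 2264 patients would provide 80% power to detect a constant Hazard ratio (HR) of 0.76 for one-year mortality" and "If one-year mortality is 30%, then 2264 patients would provide 76% power to detect a HR of 0.81". With 1132 per group, mortality in the second group is 1 − (1 − p1)^HR, and power is Φ(√events/2 × |ln HR| − 1.96).

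- 20%, HR 0.76: second-group mortality 15.6%, 403 events, power 78.7% (stated 80%).
- 30%, HR 0.81: second-group mortality 25.1%, 624 events, power 74.9% (stated 76%).

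Both agree to within two percentage points and are not in dispute. They matter here because they show the mortality and the mortality ratios that the study has in mind.

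**Effect of death on length of stay.** Assume constant daily hazards: λ for discharge alive, equal in both services, and μ for death in hospital, differing between them. All hazards are assumptions, because the documents give none.

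- Mean stay = 1/(λ + μ)
- In-hospital mortality = μ/(λ + μ)
- Chance that a two-sided 5% t test favours the service with more deaths, with 1132 per group and clustering ignored: Φ(d/SE − 1.96), where d is the difference in mean stay and SE = √((m1² + m2²)/1132) for exponential stays with means m1 and m2

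With λ = 5% per day:

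| μ per day | In-hospital death | Mean stay, days | Gap, days | t test favours the service with more deaths |
|---|---|---|---|---|
| 0.5% v 0.625% | 9.1% v 11.1% | 18.2 v 17.8 | 0.4 | about 8% |
| 1% v 1.25% | 16.7% v 20.0% | 16.7 v 16.0 | 0.7 | about 16% |
| 0.5% v 1% | 9.1% v 16.7% | 18.2 v 16.7 | 1.5 | about 54% |
| 1% v 2% | 16.7% v 28.6% | 16.7 v 14.3 | 2.4 | about 95% |

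For example, 1/(0.05 + 0.01) = 16.7, 1/(0.05 + 0.0125) = 16.0 and 1/(0.05 + 0.02) = 14.3 days. The first two rows have a death hazard ratio of 0.80, close to the plan's 0.76 and 0.81. The last two have 0.50, well beyond it. In the last row, in-hospital mortality of 28.6% would use up almost all of a 30% one-year mortality, so it is an upper illustration.

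**Leaving out the deaths.** Under these hazards the mean stay of patients discharged alive is [λ/(λ + μ)²] / [λ/(λ + μ)] = 1/(λ + μ), the same as for all patients. Excluding decedents leaves every gap in the table unchanged.

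**What a competing-event analysis shows.** The cause-specific hazard ratio for live discharge is 0.05/0.05 = 1 in every row, so the equal discharge process is correctly reported. The eventual cumulative incidence of live discharge, λ/(λ + μ), is 83.3% v 80.0% for 1% v 1.25%, and 83.3% v 71.4% for 1% v 2%. The service with more deaths no longer looks better.

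**Readmission and cardiovascular events.** Take a one-year event risk of 30% if nobody died, equal in both services, with constant hazards and one-year mortality of 20% v 30%. With h = −ln 0.7 and m = −ln(1 − mortality), the proportion with an event by one year is h/(h + m) × (1 − e^−(h + m)) = 27.1% v 25.5% (odds ratio 0.92). With complete follow-up these are the cumulative incidences with death competing, so the crude proportion is a valid quantity. Event or death by one year is 1 − 0.7 × 0.8 = 44% v 1 − 0.7 × 0.7 = 51%, which shows what the first figure alone conceals.

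**The case against.** The strongest reply is that the article is silent, not wrong. It assigns methods by data type and never says that deaths are disregarded. A Mann-Whitney test could rank deaths worst, and the full analysis plan may say so. This stands to the extent that a reader should not infer a stated decision to ignore deaths. But the methods that the article names have no death term, and under the two simplest readings (deaths at face value, deaths excluded) the problem remains.

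Four stronger readings are tempting, and the documents do not support them.

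- *That logistic regression is wrong for readmission and cardiovascular events.* The Sample size section assumes no loss before one year, and the Plan of investigation calls for complete follow-up. Under those conditions the one-year proportion already is the cumulative incidence with death competing. Preferring a cause-specific hazard is a choice of question.
- *That the composite leaves out cardiovascular death.* Its components are not restricted to non-fatal events, so a fatal recurrent stroke or infarction can count.
- *That the t and Mann-Whitney tests defeat the aim of case-mix adjustment.* Multiple regression is planned beside them, and describing variation is an objective in its own right.
- *That costs are distorted.* Lower cost after an early death is a true cost, and the economic sections pair cost with EQ-5D and QALYs, where lost survival can enter.

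It is also fair to say that the study is exploratory and disclaims causal inference, and that excess deaths would be visible in the primary analysis next to the shorter stays. That limits the harm. It does not make the length-of-stay comparison interpretable on its own.

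**Conclusion.** The point holds for acute and rehabilitation length of stay when they are read as measures of service quality. The named methods let higher in-hospital mortality appear as a shorter stay, and baseline adjustment does not prevent it. With death hazard ratios near those in the Sample size section, the spurious gap is about 0.4 to 0.7 days; at a ratio of 0.50 it is 1.5 to 2.4 days. These sizes rest on constant hazards, an assumed live-discharge rate of 5% per day and assumed in-hospital death rates. The direction is a risk only: if those who die have long stays, it could be reversed. The primary mortality analysis is not affected. For readmission and cardiovascular events the planned proportion is sound and needs only a companion endpoint.

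**What to change.** - **Length of stay as an outcome of service quality:** analyse time to discharge alive with in-hospital death as a competing event. Report case-mix-adjusted cause-specific hazards for live discharge and for death, together with the cumulative incidence of live discharge. Do this for the acute stay and for the rehabilitation stay.
- **Length of stay as resource use:** keep total bed-days, decedents included, for the cost analysis.
- **Readmission and cardiovascular events:** keep the one-year proportion and report event-or-death by one year beside it.

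The cost is modest extra analysis. The study already plans to collect mortality and length of stay from case records, with death certificates and hospital episode data, so the dates needed for the stay analysis should be at hand. The event-or-death proportion needs only each patient's status at one year, which matters because an event without an admission may have no hospital-episode date. The main drawback is that a hazard ratio for live discharge is less familiar to commissioners than a difference in days. The cumulative incidence curves help with this.

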## Background

Stroke is the third leading cause of mortality and the number one cause of long-term disability in the UK. More than 150,000 people suffer a stroke in the UK each year [1]. It costs the NHS approximately £ 7 billion per annum [2]. Stroke incidence rises sharply with age and despite better primary and secondary preventative measures, the total number of strokes is set to rise in the UK [3]. Nevertheless, stroke care in UK is far from ideal: patients having a worse outcome in terms of death and dependency than many other European countries [4-6], at least in part due to differences in care provided [7]. There is also variation in outcome between different localities within the UK [8-11], these local differences being highlighted in the most recent publication of the National Sentinel Stroke Audit in 2009 [12]. These differnces probably arise as a result of substantial variations in how the stroke services are provided across the UK. Examples of such differences are access to neurovascular/neurosurgical service, early supported discharge, and stroke specialist on call rota for thrombolysis. The presence or absence of variations in stroke outcomes as a result of variation in care and how much the observed variations in patients' outcomes including patient reported outcome measure (PROM) are determined by the differences in service delivery have not been examined previously.

We hypothesise that variation in patient outcomes including mortality, length of stay, institutionalisation rate, and patient reported outcomes between care providers can partly be explained by the different ways in which stroke services are delivered. The main objectives of the study are (1) to describe variation in outcomes following stroke and to identify the characteristics of services that are associated with better outcomes after accounting for case mix differences and individual prognostic factors, and (2) to obtain preliminary data to identify sample size and inform future pragmatic real world setting RCTs in the area of health service delivery in stroke.

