The clinical teams will retrieve case records to collect (1) baseline measures which were not recorded in baseline Network surveys and (2) outcome measures including mortality and hospital length of stay. At study commencement (October 2010) one year follow up data can be collected immediately for October 2009 cohorts (follow up complete at end September 2010). The follow up will be completed in September 2012 as the stroke patients included in the last survey for the study conducted by the Network in July 2011 will complete one year follow-up in June 2012 and data collection of the study will be completed by July-August 2012 with the view of final cohort data arrival to research team by the end of December 2012.

Due to multi-centre nature of the study the individual sites are expected to join the study at different time points (after their respective NHS Research & Development Committees' approval). We will collect characteristics of stroke services, patient related factors, prognostic indicators, treatment options and trial/study participation. Missing prognostic data will be imputed statistically, to ensure that all eligible patients are included in the primary analysis (see also Statistical Methods).

The service characteristics of interest include:

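### The stated basis for imputing missing prognostic data leaves out death, follow-up time and service, which can bias the case-mix-adjusted service hazard ratio

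*Protocol article*

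**What the plan says.** The Statistical analysis section of the protocol article gives one basis for imputation: "Missing prognostic and EQ-5 D data will be imputed, based on each patient's other prognostic characteristics". Under Plan of investigation the article says where the result is used, and refers the reader on to the statistical methods: "Missing prognostic data will be imputed statistically, to ensure that all eligible patients are included in the primary analysis".

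The model that receives the imputed values is a Cox regression "to examine the relationships between different aspects of health services and time to death, adjusting for prognostic characteristics". It serves the primary outcome (Outcome measurements): "Primary outcome of the study will be one year mortality comparison between services with different characteristics". The first objective (Background) is to "identify the characteristics of services that are associated with better outcomes after accounting for case mix differences and individual prognostic factors".

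No other section widens the imputation basis to include death, follow-up time, trust or service characteristics.

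**The concern.** An imputation model should contain the variables of the analysis it feeds. Here two kinds are not named.

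- **Outcome.** If severity, say, is imputed without reference to death, the filled-in values are unrelated to death given the other covariates. The severity coefficient in the Cox model is then pulled towards zero.
- **Exposure.** If service is left out, filled-in severity does not reflect any extra severity in one type of service. The case-mix difference between services looks smaller than it is.

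Both errors leave case mix under-adjusted. What is not adjusted away goes into the service hazard ratio: services with sicker patients look worse than they are, and services with healthier patients look better. Separating service effects from case mix is the study's main purpose, so the primary comparison is what is at stake.

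**Working it through.** **1. The plan's own power figures.** The point does not depend on them, but they fix the sample size and event rate used below. The Sample size section says that "a total sample of 2264 patients would provide 80% power to detect a constant Hazard ratio (HR) of 0.76 for one-year mortality". Its inputs are 20% mortality in the reference arm, complete follow-up and a two-sided 5% test; a second scenario takes 30% mortality and HR 0.81 and states 76% power. With two groups of 1132, p1 = 1 − (1 − p0)^HR, events = 1132 × (p0 + p1), and power = Φ(|ln HR| × √events / 2 − 1.96):

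- p0 = 0.20, HR 0.76: p1 = 0.156, events = 403, power = Φ(2.755 − 1.96) = 78.7% (stated 80%).
- p0 = 0.30, HR 0.81: p1 = 0.251, events = 624, power = Φ(2.631 − 1.96) = 74.9% (stated 76%).

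Both are within 2 points of the stated figures, so they stand.

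**2. Simulation.** From the article: 2264 patients, about 20% one-year mortality, two equal groups, adjusted Cox model. Assumed, because the article gives no values: one prognostic factor X with hazard ratio 2 per SD; a second factor Z correlated 0.3 with X; X higher by a stated gap in one service group; X missing completely at random. There were 300 replicates per setting. Multiple imputation used M = 5 with total variance W + (1 + 1/M)B, where W and B are the within- and between-imputation variances. Two imputation models are compared:

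- As written: X from Z.
- Full: X from Z, service, death indicator and Nelson-Aalen cumulative hazard.

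True service HR 1.00, gap 0.3 SD:

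| X missing | Service HR, as written | Rejection at nominal 5% | HR of X (true 2.00) | Service HR, full | Rejection, full |
|---|---|---|---|---|---|
| 10% | 1.05 | 7% | 1.85 | 1.00 | 5% |
| 20% | 1.08 | 11% | 1.71 | 1.00 | 4% |
| 30% | 1.10 | 17% | 1.60 | 0.99 | 5% |
| 40% | 1.15 | 29% | 1.49 | 1.01 | 3% |

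The Monte Carlo standard error is about 0.005 on the log hazard ratio and about √(0.05 × 0.95 / 300) = 1.3 points on a rejection rate near 5%. The 7% at 10% missing is therefore not clearly distinct from 5%, although the shift in the hazard ratio is.

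Other settings, all with 30% missing:

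- No gap: service HR 1.00 as written, although the HR of X is still diluted to 1.60.
- Gap 0.5 SD: 1.20 with 46% rejection as written; 1.01 with 5% under the full model.
- True HR 0.76, better service has the sicker patients (0.3 SD): 0.85, with power 34% against 78% on complete data; 0.765 under the full model.
- True HR 0.76, better service has the healthier patients: 0.69 as written; 0.76 under the full model.
- True HR 1.00, gap 0.3 SD, adding service alone or outcome alone: 1.05 in each case. About half the bias remains, so both are needed.

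**3. Check by hand.** Let f be the missing fraction, β = ln 2 = 0.693 and Δ the gap, and suppose Z carries none of the gap. Imputing without the outcome shrinks the coefficient to about (1 − f)β. Imputing without service shrinks the gap to about (1 − f)Δ. The part of the log hazard left in the service term is then βΔ[1 − (1 − f)²].

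- f = 0.3, Δ = 0.3: 0.693 × 0.3 × 0.51 = 0.106, HR 1.11; coefficient 0.7 × 0.693 = 0.485, HR 1.62.
- f = 0.1, Δ = 0.3: 0.693 × 0.3 × 0.19 = 0.040, HR 1.04.
- f = 0.3, Δ = 0.5: 0.693 × 0.5 × 0.51 = 0.177, HR 1.19.

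These agree with the simulation, and a reader can put in other values.

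**The case against.** The strongest reply is that this is one sentence in a one-paragraph analysis section of a journal article. It does not say that other predictors are excluded, and predictor lists, single or multiple imputation, and pooling are commonly left to a fuller plan. This stands in part. A reader might infer that the sponsor has deliberately ruled out outcome and service; the text does not say so. But the article is not silent either: it names a basis, applies the result to the primary analysis, and nowhere widens it. An analyst who follows the sentence gets the model tested above.

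The size rests on assumed inputs. That stands. Clinical teams are also to retrieve case records for baseline measures that the network surveys did not record, which should reduce missingness. At 10% missing the bias is small, and without a case-mix gap there is none in the service hazard ratio. So the rule can bias the comparison; it does not necessarily do so. If the imputation were single and deterministic, the bias at 30% missing would be smaller (HR 1.05) when missingness is equal between services.

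Two stronger readings are tempting and are not supported.

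- **EQ-5D.** The same sentence covers EQ-5D, so a reader might infer an equal fault in the economic evaluation, or that values will be imputed for patients who have died. No section says the latter. The Outcome part of the economic evaluation plans a mapping algorithm for patients without EQ-5D. The other patient-reported measures that might help belong to the same component and will often be absent together with EQ-5D. Nothing here tested EQ-5D.
- **Trusts with more missing data are adjusted least.** The calculations do not show this at trust level. One run with missingness also differing between services gave 1.10 under multiple imputation as written, the same as with equal missingness.

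Finally, the study is described as exploratory and disclaims causal inference. That lowers the stakes but does not remove them, since its output is an adjusted association.

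**Conclusion.** The point holds in conditional form. The stated imputation basis omits the outcome and the exposure of the primary Cox model. It dilutes the prognostic coefficient and, where case mix differs between services and missingness is appreciable, biases the service hazard ratio.

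Under the assumptions above, a null effect moves to between about 1.05 and 1.15 over 10 to 40% missing. At 30% the shift is ln 1.10 / |ln 0.76| = 0.095 / 0.274, about a third of the illustrative target effect on the log scale. The direction depends on which services have the sicker patients, so real differences can be hidden as well as false ones produced. The missing fraction, the gap and the prognostic effect are assumptions, and the figures illustrate the mechanism; they do not predict this study's bias. The mechanism is established well enough, and the correction cheap enough, that the sentence should be changed before analysis.

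**What to change.** Replace the sentence in Statistical analysis, as far as it concerns prognostic data, with a statement that missing prognostic data will be multiply imputed and combined by Rubin's rules. The imputation model should contain:

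- all covariates of the analysis model;
- the death indicator and the Nelson-Aalen cumulative hazard;
- either the service characteristics or a trust indicator, but not both where they are collinear: hospital-level characteristics are largely constant within each of the eight trusts;
- for secondary models, the relevant outcome.

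The cost is slightly more analysis work. These variables are already needed for the planned models, so no new data are required.
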